# **Treatment** **of Subjects**

Participants will have access to the app for 120 days following completion of the baseline survey and can complete the modules in a self-guided way that best suits them. Users will be directed to each module linearly, unlocking a new module will require completion of the previous one. Once modules are unlocked, participants can re-access them at any time. Participants in the trial can use the app as often or as little as desired. App usage data will be collected directly through the LifeBuoy app, which will include the number of modules attempted and completed.

**Trial Intervention**

[figure not shown]
The intervention being trialled in this study is called *LifeBuoy*. *LifeBuoy* is a mobile treatment app developed by researchers at the Black Dog Institute. It is a fully automated, self-guided program theoretically grounded in Dialectical Behaviour Therapy (DBT) and Acceptance and Commitment Therapy (ACT). The app was initially developed using co-design approach, with young people with a lived experience of suicide, via online surveys and focus groups. The first version of LifeBuoy was evaluated in a trial which commenced in March 2020, with preliminary findings that it did lead to greater reductions in the severity of suicidal ideation in the intervention group, relative to the control group, at post-intervention – and these gains were maintained at 3-month follow up. The version of Lifebuoy being tested in this current trial has undergone further refinements based on qualitative feedback from trial participants, and in partnership with a youth Lived Experience advisory panel, recruited specifically for this purpose. The app contains seven learning modules that are based on Dialectical Behaviour Therapy (DBT), Acceptance and Commitment Therapy (ACT), and CT and incorporates wise mind principles (distress tolerance, emotion regulation/mindfulness, interpersonal effectiveness) through interactive learning exercises to help young people develop strategies and problem-solving skills for managing suicide thoughts.

The app also includes a ‘check-in’ feature that auto-appears when a user accesses the app for the first time each day or is accessible through the home screen. The check-in asks users how they are feeling today and if they select a negative mood, they are directed toward their safety plan, crisis contact numbers, and calming/distracting activities.

Participants will download the LifeBuoy app from the App Store or Google Play onto their personal smartphones. Once the app is downloaded, it will not require internet connection; internet connectivity will only be required to upload usage and adherence data to UNSW servers.

Participants will have access to the app - to complete seven modules - until the end of the 120 day trial period. Each module will take approximately between five to ten minutes to complete. The user will be directed to each module linearly and unlocking a new module will require completion of the previous one (this also is the gamification of the app, as island ‘light up’ or become technicolour when complete). Once modules are unlocked, participants can re-access them at any time.

In addition to the LifeBuoy app, this study is seeking to trial a multicomponent digital engagement strategy aimed at increasing compliance with the LifeBuoy app. The engagement strategy will be comprised of 3 core components:

1. An Instagram account that will deliver brief, visual content that aligns to the strategies and educational information within the app itself.
2. A clinician-written blog that will provide a platform to deliver in-depth therapeutic information and advice for maintaining mental health.
3. Emails: weekly emails will be sent to participants with links to strategies 1 and 2, to remind them to visit them and in addition, the emails will suggest to participants what module within the app they might like to visit/explore that week and strategies for getting the most out of it.

The decision to leverage these specific platforms was derived from a bottom-up approach, where we have spent almost 18 months gathering information and perspectives from young people with a lived experience of suicide. The sources of data include: qualitative interview feedback from participants in the first LifeBuoy trial (HC190764); (ii) data from a broad online survey of 260 mental health app users in Australia (HC200616) (iii) and input from a youth lived experience project advisory group (HC210038). The content and design for the Instagram and blog posts is being developed in consultation with the youth lived experience project advisory group, all of whom were participants in the first LifeBuoy trial.

To deliver on the engagement strategy, Instagram posts will be uploaded at least once a week throughout the duration of the study, up till 30 days after recruitment of the final study participant. The Instagram account will be public, with comments disabled, as public access allows users to view content anonymously (otherwise they will need to register to view the account, which may be perceived as a barrier to engagement).

For the blog, new articles will be posted once a week throughout the duration of the study, again, up to 30 days following the recruitment of the final participant.

# **Types of Safety and Monitoring**

Assessment of Safety Event Report Forms

Safety reports will be assessed on the seriousness, causality, and expectedness of the event to the trial treatment(s), intervention(s), investigational medical product(s), investigational medical device(s). The following are known and expected adverse effects, harms, risks or discomforts associated with trial procedures, treatments or interventions.

Known Adverse Effects

An individual scoring above 20 on the SIDAS at any timepoint will be considered an expected adverse event (given the study population has a history of recent suicidal ideation).

Known Harms, Risks or Discomforts

Anxiety induced by answering a questionnaire and/or engaging in therapeutic activities on the app, and the cessation of updates from the digital engagement strategies at the end of the data collection phase. There is a moderate likelihood and low severity of this discomfort occurring, given the more than low-risk population participating in the study.

Psychological harms, including feelings of distress or anxiety, for example, due to disclosure of sensitive information on questionnaires and/or engaging in therapeutic activities on the app. There is a moderate likelihood and low severity of this discomfort occurring, given the more than low-risk population participating in the study.

Adverse Events or Adverse Reactions: general definitions

Adverse events (AE) are considered any untoward medical occurrence in a clinical trial participant administered the intervention, which does not necessarily have a causal relationship with this treatment.

Adverse Reactions (AR) are considered untoward and unintended responses that is related to the trial intervention or intervention procedures.

AEs and ARs are assessed using the safety monitoring flow chart. Those classified as "not serious" are assessed by the qualified physician/medical expert specified in section 2 of the protocol. The Qualified Physician cannot delegate this responsibility to other research personnel.

Adverse event reports must be reported to the Coordinating Principal Investigator within 24-hours. All adverse event reports must be recorded in the [UNSW Safety Monitoring Register Template](https://research.unsw.edu.au/document/UNSW%20Safety%20Monitoring%20Register%20Template.xlsx).

Serious Adverse Events

In this trial a Serious Adverse Event (SAE) is o one or more of the following events and the event is not related to the trial intervention:

1. A participant reporting a suicide attempt or NSSI that requires medical care at any follow-up assessment time point.
2. If we become aware of a death of a participant during the trial, for any reason, this will also be considered a serious adverse event.

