# **Sample Size**

The plan is to enrol 669 subjects to this trial. Sample size calculations were based on the primary aims. For Aim 1, to detect an expected minimum effect size of d=0.45 between the LifeBuoy intervention and the control condition on the primary measure of suicidal ideation (SIDAS), determined from the prior LifeBuoy trial (paper in review), with α = 0.01, power = 0.95, and assuming a 0.50 correlation between repeated measures, 112 subjects are needed in each condition. As a three-arm trial, with a 1:1:1 allocation, this means N=336 subjects are required to detect this effect. In addition, assuming an attrition rate of 25% in each group at our 30-day assessment based on the previous trial of LifeBuoy, 450 participants are needed (150 in each arm, rounded up). This sample size is sufficient to detect the expected effects associated with primary aim 1. For Aim 2, our recent systematic review of the engagement literature yielded three studies which were similar in design and population to our study34-36. The effect sizes in these studies varied from d = .04 to .53 reflecting a difference in user engagement when comparing a digital intervention only and the same digital intervention with an engagement strategy. Given the small number of studies, there is insufficient information to assume that effect sizes are normally distributed. Thus, the median effect size among the 3 studies (d = .38) was used as a benchmark. To detect an effect size of d=0.38 for primary aim 2 (alpha 0.01, power 0.95, assuming a 0.50 correlation between repeated measures, and 25% attrition), 223 participants are needed in each arm (rounded up). With a 1:1:1 allocation, this means N=669 subjects are required. Therefore, the larger sample size of 669 participants will be chosen to meet requirements of both primary aims. Qualitative interviews with 40 young people from the LifeBuoy and LifeBuoy + engagement group (minimum of 20 participants from the latter) will be recruited at the 30-day assessment time point, in which they will be asked whether they are interested to take part in an interview about their experience of the app and engagement strategy. This sample size will be large enough to reach saturation of qualitative themes.

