**Safety Analyses**

Suicidal behaviour (ideation, attempts, and NSSI)

- Suicidal ideation, as measured by % scoring >20 on the SIDAS
- A suicide attempt during the trial identified at all follow up surveys: “Since the last LifeBuoy study survey, how many times have you made an attempt to kill yourself in which you had some intent to die?” >0 (T1 – T3) or ad hoc self-report by participants to research study email.
- Non-suicidal self-injury during the trial identified at all follow up surveys: “Since the last LifeBuoy study survey, how many times have you injured yourself on purpose without suicidal intent (i.e., intentional, self-inflicted damage to the surface of the body but with no intent to die)?” >0 (T1 – T3) or ad hoc self-report by participants to research study email.
- Serious adverse events (including all events requiring medical intervention).
- Enrolment data, intervention completion data, attrition data, adverse event data, and other administrative data.

The TSG cannot access the unblinded data for suicidal ideation, attempt, or NSSI as these are outcome measures and will be shared only in a closed session.

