# **Risk Management Protocol**

**Estimated flag and call-back rates**

Trial one, LifeBuoy study: 455 participants completed baseline; 259 were flagged (i.e., scored SIDAS >20); and 5/259 (1.93%) requested a call back from the team clinical psychologist.

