**Flagging procedure**

**1)** At each survey timepoint (baseline, 30-days, 60-days, and 120-days) three items indicates risk of suicide. When a selection is made indicating a concerning level of suicidal thinking (SIDAS score >20), a suicide attempt during the trial, or NSSI requiring medical care during the trial, an automated alert system is triggered, where an automated email is sent to the participant asking if they would like to receive a phone call from the team clinical psychologist during business hours (9:00 to 17:00 AEST) within the next 3 working days. This email will also include a list of crisis contact numbers for support.

*“Hi there,*

*Thanks so much for signing up to participate in the study and for completing the latest survey. We noticed that your responses on the survey indicate a recent self-harm event or severe current suicidal thoughts. If you would like to receive a phone call from our clinical psychologist during business hours (9:00 to 17:00 AEST) within the next 3 working days, please click ‘reply’ to this email or send a new email request to [contact]*

*If you’ve had a tough time with your mental health lately, we encourage you to talk to a local doctor or mental health professional about how you’re feeling. If you would like to know where to get some immediate help, here are some suggestions:*

- *Lifeline: [name]*
- *Kids Helpline :[name]*
- *Suicide Callback Service: [name]*

*For 24-hour advice on what to do and who to contact, don’t hesitate to visit HealthDirect (https://www.healthdirect.gov.au) or call them at [name]).*

*If you feel in danger or that you might hurt yourself, do not hesitate to call Emergency Services on 000.*

*Warm regards*

*The LifeBuoy team”*

(*Note:* at the completion of each survey all participants will be shown a screen with the same abovementioned support contacts).

**2)** If a flagged participant indicates they would like a call back, the team clinical psychologist ([name]) will contact the participant via phone as soon as possible. This discussion will centre around making sure the young person is supported in their family and/or community and identifying how they can access the services they need. If the participant expresses distress in relation to using the app or answering the assessment questionnaires, they will be reminded of their right to withdraw from the trial without penalty or the need for explanation.

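### The ideation adverse event takes in baseline scores, contrary to the protocol's own definition of an adverse event; on the first trial's figures about 381 of 669 participants would be counted before any exposure

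*Protocol*

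**What the plan says.** The rule is in the protocol under Types of Safety and Monitoring, Known Adverse Effects: "An individual scoring above 20 on the SIDAS at any timepoint will be considered an expected adverse event". The reason given for calling it expected is that the study population has recent suicidal ideation.

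A little further on, the general definitions describe an adverse event as "any untoward medical occurrence in a clinical trial participant administered the intervention".

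The Risk Management Protocol, Flagging procedure, lists the timepoints: "At each survey timepoint (baseline, 30-days, 60-days, and 120-days) three items indicates risk of suicide". Treatment of Subjects starts the 120 days of app access once the baseline survey is complete.

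The same appendix reports the first LifeBuoy trial: "455 participants completed baseline; 259 were flagged (i.e., scored SIDAS >20"), and of those flagged, "5/259 (1.93%) requested a call back from the team clinical psychologist".

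In the DSMB charter, Safety Analyses, the ideation measure is "Suicidal ideation, as measured by % scoring >20 on the SIDAS". It uses the same cut and makes no reference to the participant's starting score.

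**The concern.** Two sentences in one section give different answers for the same observation. A score above 20 at baseline meets the specific rule but fails the general definition, because the participant has not yet had the app. The safety section also asks for each report to be assessed for causality, a question with no meaning before exposure.

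The rest of the plan does not share the problem. Survey-reported serious adverse events (a suicide attempt, or self-injury needing medical care) are limited to follow-up assessments, and the charter's attempt and self-injury measures are limited to T1 to T3. Only the ideation event lacks that limit.

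The rule is also a fixed cut on the primary outcome scale, applied to people enrolled because they have suicidal thoughts. It says whether someone is above 20, not whether they have become worse. An adverse event count built on it would mix entry severity, persistence, improvement that stops short of 20, and true deterioration. The reporting duties attached to adverse events (notice to the Coordinating Principal Investigator within 24 hours, entry in the register, assessment by a physician who may not delegate) would on a literal reading attach to the baseline scores too.

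**Working it through.** **Inputs.** From Estimated flag and call-back rates: 455 completed baseline, 259 flagged, 5 call-backs. From Sample Size: N = 669, 25% attrition, correlation 0.50 between repeated measures. From the SIDAS scoring note: range 0 to 50.

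**1. The plan's own figure.** 5/259 = 0.0193, or 1.93%. This reproduces.

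**2. Share above 20 in the first trial.** 259/455 = 0.569, or 56.9%. The Wilson 95% interval is 52.3% to 61.4%.

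**3. Scaled to this trial.** 669 × 0.569 = 381. The limits are 669 × 0.523 = 350 and 669 × 0.614 = 411. With the event limited to follow-up, the baseline count is 0.

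**4. Dependence on reading the 259 as baseline flags.** That is the natural reading, but the text does not say it outright. Half of 455 is 227.5, so the share falls to half or below only if at least 259 − 227 = 32 of the flags first arose later.

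**5. What the cut counts at follow-up.** On the 0 to 50 scale, a fall from 45 to 21 is an adverse event and a rise from 3 to 20 is not. This follows from the wording alone. How common such cases would be cannot be taken from the document, which gives no SIDAS standard deviation. As an illustration, assume normal scores rounded and clipped to 0 to 50, 56.9% above 20 at baseline, SD 8 to 12, baseline-to-T1 correlation 0.5 to 0.7 and a mean fall of 0.25 to 0.5 SD. Then 40% to 58% of those counted at T1 have a lower score than at baseline, and 25% to 35% of those who worsen by 5 points or more are not counted.

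**6. Does the cut hide harm between arms?** Keep those assumptions and let one arm be worse by a uniform 0.3 SD, with 223 × 0.75 = 167 per arm. A baseline share of 56.9% puts the mean 0.174 SD above the cut.

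- Mean fall 0.25 SD: Φ(0.174 − 0.25) = 0.470 against Φ(0.174 − 0.25 + 0.3) = 0.589. The standard error is √[(0.470 × 0.530 + 0.589 × 0.411)/167] = 0.054, so z = 0.119/0.054 = 2.2.
- Mean fall 0.5 SD: 0.372 against 0.490, and again z = 2.2.

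Expected z for the possible measures at T1:

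| Measure | r = 0.5 | r = 0.7 |
|---|---|---|
| % above 20 | about 2.2 | about 2.2 |
| New crossing only | 1.3 to 1.4 | 1.4 to 1.5 |
| New crossing or rise of at least 5 points | 1.9 to 2.1 | 2.2 to 2.6 |

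At the protocol's own correlation of 0.50 the existing percentage does at least as well as either change-based measure. At 0.7 the combined measure gains modestly. Harm confined to a subgroup could behave differently.

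**The case against.** The best defence is that an absolute, over-inclusive cut is a conservative choice, and that the protocol already labels the event as expected in this population. The label settles expectedness. It does not make a score recorded before exposure an occurrence under the intervention, so the contradiction stands.

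A reader might infer that harm caused by the app would be diluted or invisible to the DSMB. The documents do not support that. The charter supplies the percentage above 20, not a tally of anyone ever above 20, and meetings follow each assessment point. Randomisation balances baseline severity in expectation, so the follow-up percentage by arm is a fair comparison, and step 6 shows it is not an insensitive one. Attempts, self-injury and serious adverse events are reported separately, and closed sessions can see unblinded SIDAS data with effect sizes. SIDAS is also analysed longitudinally as the primary outcome.

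A reader might also infer a flood of reports within days, since Recruitment Strategy mentions an earlier app trial that recruited more than 450 people in four days (450 × 0.569 = 256). That borrows another trial's pace. The flow chart that governs how reports are raised is not shown, the alerts are automated, and single reports need not go to the sponsor's delegate or the ethics committee.

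Finally, one might want to replace the cut with a change-based rule. That would take participants who stay severe throughout out of the physician assessment that adverse event status brings. The objection is sound, and it limits the remedy to clarifying and adding.

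**Conclusion.** The point holds as an internal contradiction with a sizeable effect on a count. Read literally, the rule records about 381 of 669 participants (350 to 411) as adverse events before they have the app. This projection rests on two assumptions: that the 259 earlier flags were baseline flags, and that the new sample resembles the earlier one. The interval reflects sampling error only.

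The adverse event tally would therefore largely record entry severity, and at follow-up it would include people whose scores have fallen but are still above 20. It should not be read as a measure of deterioration. The percentages in step 5 are illustrative, because the document gives no SIDAS standard deviation.

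The consequence stops there. The DSMB keeps valid means of seeing harm, and no primary estimate, error rate or sample size is affected.

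**What to change.** - **Types of Safety and Monitoring.** Reconcile the two sentences by counting the ideation adverse event on the follow-up surveys (T1 to T3) only, as the protocol already does for survey-reported serious adverse events. Report a baseline score above 20 as a baseline characteristic, by arm.
- **DSMB charter, Safety Analyses.** Beside the existing percentage above 20, add the proportion in each arm who have worsened from their own baseline, by a margin the sponsor fixes in advance. Do not replace the existing measure.
- **Leave unchanged** the above-20 alert to participants at every survey, baseline included, and the assessment of follow-up scores above 20.

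The cost is a few lines of protocol and charter text and one variable derived from data already collected. Adverse event counts may not be comparable with the first LifeBuoy trial if that trial counted baseline scores. Baseline scores would also no longer reach the physician through the adverse event route. Whether they should be reviewed by some other route is a clinical decision for the sponsor, to be stated separately from the adverse event definition.

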#### **Serious Adverse Reaction**

To assess whether the serious adverse event was related to the trial or intervention, participants who report a recent suicide attempt or NSSI that required medical care at any follow-up assessment time points will be asked a follow-up question: “Do you think that participating in this study or using this app has contributed to any recent distress leading you to self-harm?”

A serious adverse reaction by its nature, incidence, severity, or outcome is anticipated and identified in the current version of the intervention safety information are classified as a SAR report. SAR reports are reported to the Coordinating Principal Investigator within 24-hours for multicentre clinical trials. Serious Adverse Reaction reports must be recorded in the [UNSW Safety Monitoring Register Template](https://research.unsw.edu.au/document/UNSW%20Safety%20Monitoring%20Register%20Template.xlsx).

